##### Sampling

Surveys will be undertaken in 3600 adults in Fiji (Viti Levu) in year 1 and 4, and in Samoa (Upolu) in years 2 and 5. We have selected the main islands based on prohibitive cost and time associated with travelling to the outer islands. The samples will be stratified into equal numbers of men and women in two age groups (18–44 and 45–69 years). The sampling strategy will be based on the recent National Nutrition survey (NNS) in Fiji and the most recent WHO STEPS project in Samoa [50]. Each used a two-stage sampling process, based on census information, to obtain representative samples for selected regions. Sampling in Fiji will also be stratified by the two main ethnic groups (Indigenous Fijians, and Indo Fijians). The age, sex and region of randomly selected individuals that do not wish to participate will be recorded, such that response rates and the likely impact of non-response can be estimated.

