##### Sample size and power for evaluating impact of food policies

To determine the sample size for salt, we have used the standard deviation from recent surveys in Fiji and Samoa (SD: 3.6) which used urine collection [51], with the knowledge that the standard deviation is likely to be lower using a dietary questionnaire [52], which would mean our sample size calculation will be conservative We have estimated the standard deviation of the proportion of dietary energy from free sugar (SD: 5.4) from a recent large survey (the 2011 Australian Health Survey). With a design effect of 1.5 to account for clustering and stratification, we will need 300 participants in each country at each time-point to reach 0.9 power with a t-test to detect a 1.2 g reduction in salt consumption. For free sugar we estimated that we have 0.9 power to detect a change of 1.8% absolute decrease in the proportion of dietary energy from free sugar between time points. A response rate of about 50% is anticipated, based on our previous work in these settings [53], so 600 individuals will be approached in each country.

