##### Survey procedures

The dietary survey will be a 24 h recall using the multiple pass method [54]. Trained research assistants will use supportive visual tools showing portion sizes for locally-appropriate foods to improve accuracy. Pilot testing of this approach will be undertaken by the research assistants. Discretionary salt intake will also be estimated using previously tested methods [55]. The dietary survey data will be entered into FoodWorks nutrition analysis software [56] using established standard procedures. The FoodWorks program has already been adapted to contain Pacific Island food composition data. The parallel food composition (FoodSwitch [57]) surveys in the two sites (see 2.3 below) will provide more up to date nutrient content data processed foods and these will be incorporated into the FoodWorks dataset. The FoodWorks software enables both an overall estimate of salt and sugar intake as well as the main sources of salt and sugar in the diet.

The *primary outcomes* for the dietary surveys will be gender-disaggregated average levels of sodium and sugar intake levels for adults, and any changes during the study. Key secondary outcomes will be the main sources of sodium and sugar in the diet. Population estimates will be obtained by weighting according to the sample design and the age/gender population structure based on Census data. The results will also be reported for major participant subgroups defined by sex, age and ethnicity (Fiji only) and evidence for differences between subgroups examined using t-tests.

*Reporting results to participants* - The summary results of the 24-h diet recall survey will be distributed to all participants who expressed interest in receiving the results by either email or postal address as part of the consent process. The information provided will include estimated population daily sodium and sugar intakes and how this compares to current national guidelines for salt and sugar. This will be accompanied by simple advice about how to eat a healthy diet low in salt and sugar and high in fruit and vegetables. Phone and email support will be available for 12 months after the last of the baseline and follow-up results letters have been dispatched.

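### The t-tests named for subgroup differences do not carry over the survey's weights and clustering; as ordinary t-tests their type I error would run from about 5% to about 11%, depending on the subgroup.

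*Protocol article*

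**What the plan says.** Four statements in the Methods of the protocol article, all on the 24-h diet surveys, bear on this point.

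- **Sampling.** The design follows earlier national surveys in the two countries: "Each used a two-stage sampling process, based on census information, to obtain representative samples for selected regions". The sample is stratified into equal numbers by sex and two age groups (18–44 and 45–69) and, in Fiji, also by the two main ethnic groups.
- **Sample size and power for evaluating impact of food policies.** The calculation is made "With a design effect of 1.5 to account for clustering and stratification". It is framed as a t-test of the change in a country's mean between two time points.
- **Survey procedures, estimates.** "Population estimates will be obtained by weighting according to the sample design and the age/gender population structure based on Census data".
- **Survey procedures, tests.** The next sentence says that results will be reported by sex, age and ethnicity (Fiji only), with "evidence for differences between subgroups examined using t-tests".

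The article gives no cluster size, number of clusters, intracluster correlation (ICC), weights, or design effect for any subgroup contrast.

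**The concern.** The protocol recognises the complex design when it sets the sample size and when it forms the estimates, but not where it names the subgroup test. An ordinary two-sample t-test treats observations as independent and equally weighted. That raises two separate problems.

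1. **Different quantity.** Equal allocation to the age groups need not match the census, which is presumably why the estimates are weighted. An unweighted t-test could then give a p-value for a difference other than the one printed in the table.
2. **Wrong variance.** People in the same cluster tend to eat alike. If a subgroup contrast is largely a contrast between clusters, the ordinary standard error is too small and false positives become more frequent. Ethnicity in Fiji is the named subgroup most exposed to this.

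Elsewhere the article does say how dependence is handled: for the food composition data it specifies mixed models that allow for repeated measurements. The diet-survey subgroup tests have no such qualifier.

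**Working it through.** **Inputs from the article:** design effect 1.5; 300 participants per country per time point; salt SD 3.6 and difference 1.2 g; free-sugar SD 5.4 and difference 1.8 percentage points; power 0.9.

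**Assumed:** two-sided α of 0.05 (not stated); cluster sizes m of 10, 20 and 30; and an ICC set so that the overall mean has a design effect of 1.5, that is ICC = 0.5/(m − 1).

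**Step 1: the plan's own figure.** Salt: n = 2 × (1.960 + 1.282)² × (3.6/1.2)² = 189.1, so 190 per time point. Multiplied by 1.5 this is 285, and 300 is consistent with rounding up. At 300 the effective size is 300/1.5 = 200, and power = Φ(1.2/(3.6 × √(2/200)) − 1.960) = Φ(3.333 − 1.960) = 0.915. Sugar has the same standardised difference (1.8/5.4 = 1.2/3.6), so the same power. The design effect is therefore applied in the calculation for the change between surveys.

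**Step 2: an unadjusted test when the contrast itself has design effect D.** Type I error = 2 × [1 − Φ(1.960/√D)]. For D = 1.5 this is 2 × [1 − Φ(1.600)] = 0.1095, and the ordinary standard error is 1/√1.5 = 0.816 of the correct one (18% too small).

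| D of the contrast | 0.9 | 1.0 | 1.1 | 1.2 | 1.3 | 1.5 |
|---|---|---|---|---|---|---|
| Type I error | 3.9% | 5.0% | 6.2% | 7.4% | 8.6% | 11.0% |

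**Step 3: which D applies to a subgroup contrast.** Take two equal subgroups and a common cluster effect. In half the clusters one subgroup makes up a share p, and in the other half a share 1 − p. With d = 2p − 1, the design effect of the difference is D = 1 − ICC + d² × m × ICC.

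- Balanced within clusters (d = 0): the cluster effect cancels and D is just below 1.
- Split 80/20 (d = 0.6): D is 1.14 to 1.17.
- Whole clusters (d = 1): D = 1 + (m − 1) × ICC = 1.5.

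A simulation of unadjusted t-tests (300 people, 20,000 replicates) agrees with the formula. Formula values are in brackets.

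| Cluster size (ICC) | Balanced within clusters | Split 80/20 | Whole clusters |
|---|---|---|---|
| 10 (0.056) | 4.4% (4.4%) | 6.7% (6.7%) | 11.2% (11.0%) |
| 20 (0.026) | 4.9% (4.7%) | 6.7% (6.9%) | 11.0% (11.0%) |
| 30 (0.017) | 4.9% (4.8%) | 7.0% (7.0%) | 11.3% (11.0%) |

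The number surveyed does not enter the formula. The Sampling section's figure of 3600 adults, which sits oddly with 300 needed and 600 approached per country, therefore does not change these percentages.

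**Step 4: unweighted against weighted difference.** Suppose the four sex-by-age cells are equal in the sample, and the younger group is a share w of each sex in the population. The unweighted sex difference then departs from the weighted one by (0.5 − w) × (sex difference in the young − sex difference in the old). This is zero if w is one half or if the sex difference is the same at both ages. The article gives neither quantity, so the gap cannot be sized.

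**The case against.** A reader might infer that all the subgroup tests run at about 11%. The article does not support that. The 1.5 is a planning value for a country mean compared between time points, not for subgroup differences. Men and women, and younger and older adults, normally occur in the same clusters, so the shared effect largely cancels and clustering alone leaves the error at or slightly below 5%. No ethnicity test is planned in Samoa.

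A reader might also infer that the tests are stated to ignore the design. They are not. The sentence before describes design weighting, and the power section pairs a t-test with the design effect, so a design-adjusted t-test is a possible reading. For the same reason, the power section cannot show that the test of change between surveys disregards clustering. It is a power statement, not an analysis specification.

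Finally, this is a condensed article, and the way standard errors are computed is often left to an analysis plan. That argument would succeed if the article were silent. It is not silent: it names a test which, in its ordinary meaning, fits neither the weighted estimates nor the clustered variance. The objection narrows the size of the point and leaves the need for clarification standing.

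**Conclusion.** The point holds in limited form. The named subgroup test does not carry over the weights and clustering that the article recognises elsewhere. If the tests are run as ordinary t-tests, they may test differences other than the weighted ones reported, by an amount that cannot be calculated from the article. Type I error from clustering would be about 5% for subgroups balanced within clusters, about 7% for an 80/20 split, and about 11% for subgroups made up of whole clusters. The last case would apply to ethnicity in Fiji only if villages are ethnically homogeneous, which the article does not say.

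These figures rest on an overall design effect of 1.5, a two-sided 5% level, and assumed cluster sizes and ICCs. Any effect of unequal weights on the variance is left out, because no weights are given. This is worth correcting, but it concerns subgroup comparisons and does not show that the primary analysis of change is wrong.

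**What to change.** In Survey procedures, replace the t-tests with design-based tests: survey-weighted regression, or the equivalent Wald or t-tests, using strata, primary sampling units and final weights with linearised or cluster-robust variance. Take the reference degrees of freedom from the design (primary sampling units minus strata), because the number of clusters may be small: 300 people in clusters of 30 is only 10. State that the change between surveys is tested with the same design-based variance, so that the analysis matches the sample size calculation.

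The cost is a change of wording, a little more analysis work, and keeping stratum and cluster identifiers in the data set. The Strengths and limitations section says that the community dietary surveys could not yet begin, so this could be settled before data collection. Intervals will usually be slightly wider for between-cluster contrasts, by at most √1.5 = 1.22 times where the contrast has a design effect of 1.5, and little changed or slightly narrower for contrasts balanced within clusters.

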#### Assessing food composition and price of processed foods

The objective of this survey is to measure and assess changes in salt and sugar levels in foods. For this, a standardised approach and a smartphone application will be used to collect data. FoodSwitch is a smart phone application originally developed in Australia and since launched in 7 other countries including the United Kingdom, China and India [57]. The FoodSwitch App can be used to collect food composition data based on back of pack Nutrient Information Panel, which is uploaded into a comprehensive database of nutrition composition. Salt and sugar levels and prices of processed foods in the market will be assessed in years 1 and 4 (2 and 5 for Samoa) at a similar time to the dietary surveys. Data will be collected from the shops that collectively provide the majority (more than 80%) of the processed foods available for purchase in Fiji and Samoa, using the same sampling strategy each year. Food products will be categorised using the existing FoodSwitch food categorisation system. The data fields collected for each product will be brand/manufacturer, product name, food category, serving size, sodium, total fat, saturated fat, and sugar per 100 g. The FoodSwitch App will be used to take photos of the front and back of the pack. Data are then extracted from pictures of the Nutrient Information Panel on the back of packs and inputted by data assistants. Brand/manufacturer name will be recorded in order to establish the proportion of packaged products that are imported compared to the proportion that are produced locally. Price data will be recorded separately. Lists of ingredients will also be recorded.

##### Data analysis and sample size

Mean levels of salt and sugar, overall and by product category, and individual product prices and mean prices for each product category for year 1, 3 and 5 will be calculated. Based on the 2013 processed food composition database, it is expected that data on around 1200 products will be collected each year. We will estimate the paired change in salt and sugar levels between baseline data and each of the follow-up points. Even if the percentage change in composition is highly dispersed (e.g. SD = 20) we should have 0.9 power to detect a 1% change in composition across all categories, or a 10% change for food categories with 50 items. We will analyse the change over time using linear mixed models which account for the repeated measurements.

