**Fig. 1 Fig1:**
[figure not shown]
Study design based on type 3 effectiveness-implementation hybrid trial

The interventions will be staggered so that one country can provide comparison data during the first year, and we will use publicly available data (e.g. WHO Stepwise risk factor (STEPS) survey and the Household Income Expenditure Survey (HIES), as well as data from other national cross-sectional surveys, to understand policy impact.

Main outcome measures: changes in population intake levels of salt and sugar, salt and sugar levels in foods, and food prices (measured through surveys done at baseline and follow-up). Changes in blood glucose and blood pressure and overweight/obesity (measured in consecutive STEPS surveys).

Main process measures: reach, adoption, implementation (context, costs and adaptations made during delivery) of the implemented food policies.

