### Systems thinking in community knowledge exchange (STICKE)

Building on the previous work done in Fiji [58], and informed by baseline outcome data and the policy landscape analysis, we will invite key government, industry and civil society leaders to participate in a structured, facilitated process [59] to build consensus on population level actions to reduce sugar and salt. We will engage 15–20 participants in each country, recruited through known contacts of the existing project team, in a series of deliberative consensus building forums. The objectives will be to understand diets and the drivers of poor diet, map existing interventions, and then discuss barriers and opportunities to strengthening policy implementation.

We will use techniques adapted from community based participatory system dynamics, notably group model-building and software (STICKE), to engage stakeholders in building a causal loop diagram reflecting the complexity of the drivers of unhealthy food availability and consumption and identify new or adapting existing interventions to reduce salt and sugar. Specific food policy interventions identified through a preliminary stakeholder meeting in January 2020 include:Taxes on foods or drinks high in salt or sugar – we will identify steps that need to be taken to strengthen existing implementation, including amending the level or type of taxation or extending to other foods.Programs to influence the nutrient content of available processed foods - we will identify new policies or opportunities to strengthen implementation of existing policies including engaging industry on reformulation or by working with importing agencies to change the balance of imports (i.e. having nutrient content restrictions to specify which foods that can be imported).School food policies and programs - we will review existing programs and identify opportunities to strengthen implementation and broaden reach including through training and capacity building and the strengthening of monitoring and accountability mechanisms.

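### Food price is a main outcome, but the stated price measure cannot separate a policy effect from general inflation or from changes in pack size and product mix

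*Protocol article*

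**What the plan says.** The main outcome measures, listed in the Methods after Fig. 1, are "changes in population intake levels of salt and sugar, salt and sugar levels in foods, and food prices", measured by surveys at baseline and follow-up. Blood glucose, blood pressure and overweight are added from other surveys.

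Taxes are one of three candidate policies in the section on systems thinking (STICKE). The work there may include "amending the level or type of taxation or extending to other foods".

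The section on assessing food composition and price lists the product fields as "brand/manufacturer, product name, food category, serving size, sodium, total fat, saturated fat, and sugar per 100 g". Net pack weight or volume is not among them. The same section says that the front and back of each pack are photographed, that price is recorded separately (without describing the price fields), and that the shops covered supply more than 80% of the processed foods on sale.

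Under Data analysis and sample size, the price quantities to be calculated are "individual product prices and mean prices for each product category". The paired-change sentence names only salt and sugar levels, and the power statement concerns composition.

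The survey years differ between two adjoining sections. One says that "prices of processed foods in the market will be assessed in years 1 and 4 (2 and 5 for Samoa". The other says that "mean prices for each product category for year 1, 3 and 5 will be calculated".

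**The concern.** Price is the direct route by which a tax acts, so a change in price is a natural early sign that a strengthened tax is working. But shelf prices also move for other reasons. General inflation raises them. A smaller pack at an unchanged price is a real unit-price rise that a shelf price does not show. A shift towards larger or dearer products moves a category mean even when no single product has changed price.

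The stated measure has nothing that separates these causes. The impact evaluation uses the baseline and monitoring surveys within each country. The staggered start offers the other country as a comparison for the first year only. With price surveys in years 1 and 4 in one country and 2 and 5 in the other, neither country has an untreated follow-up price survey over the same interval. The article itself expects economic disruption from COVID-19 during the project (Abstract and Significance), so a moving general price level is foreseeable.

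What is at stake is how one of the main outcomes is interpreted. A rise in mean price could be policy, inflation, pack mix or all three, and a flat mean could hide a real unit-price rise.

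**Working it through.** The article gives no sample size, power or effect size for price, so there is no price figure to reproduce. The figures in that section (SD 20, about 1200 products, 50 items in a category) are for composition change. As a check, taking a two-sided 5% level (not stated in the article), a 10% change in 50 items has power Φ(10/(20/√50) − 1.96) = Φ(1.58) = 0.94, in line with the stated 0.9. A 1% change in 1200 products has Φ(1/(20/√1200) − 1.96) = Φ(−0.23) = 0.41, which is not. That shortfall is a separate matter and the price point does not depend on it.

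**1. Inflation drift with no policy effect.** The inflation rate is not in the documents. I assume 1%, 3% and 5% a year. Drift = (1 + r)^years − 1.

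| Rate per year | 2 years | 3 years | 4 years |
|---|---|---|---|
| 1% | 2.0% | 3.0% | 4.1% |
| 3% | 6.1% | 9.3% | 12.6% |
| 5% | 10.3% | 15.8% | 21.6% |

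The three-year column follows the schedule in the survey section (1 to 4, or 2 to 5). The two- and four-year columns follow the years in the analysis section (1 to 3, and 1 to 5). The drift is present on either schedule.

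**2. Is the drift large against what the survey could detect?** This needs an SD for percentage price change, which the documents do not give. Borrowing the composition SD of 20 as an assumption, the change detectable with 0.9 power in paired data is (1.960 + 1.282) × 20/√n:

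- n = 1200: 3.242 × 0.577 = 1.87%
- n = 50: 3.242 × 2.828 = 9.17%

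Over three years, inflation of 1% a year (3.0%) already exceeds the first figure, and 3% a year (9.3%) slightly exceeds the second.

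**3. Pack size.** If a pack goes from 500 g to 400 g at the same shelf price, the unit price becomes 500/400 = 1.25 times the old one. That 25% rise appears as zero in a product price with no weight or volume attached. Serving size does not supply the missing denominator unless the number of servings per pack is also known, and that is not a listed field.

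**4. Cost of a comparison category.** For 50 targeted products against the other 1150, with the same assumed SD and independent products, SE = 20 × √(1/50 + 1/1150) = 2.89. The detectable difference is 3.242 × 2.89 = 9.37%, against 9.17% without a comparator. Products of one brand or importer are likely to move together, so the true interval would be wider than this, with or without the contrast.

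**The case against.** The strongest reply is that this is a condensed article. Deflating prices, forming unit prices and choosing contrasts are things a fuller protocol or analysis plan might well contain. The text never calls its prices nominal or unadjusted. The price fields are recorded separately and not described, so pack size may be among them. It may also be readable from the photographs. Untaxed products are already in the survey. The taxed or targeted categories cannot be named yet, because the policies are chosen in later forums.

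Much of this stands, and it limits the claim. A reader might infer that the plan compares nominal prices and will read ordinary inflation as a tax effect. The article does not support that. It only calculates prices and category means, it specifies no test of a tax effect on price, and the impact evaluation section does not name price. Nor is it shown that unit prices could not be formed. Probabilities of a false-positive price rise can be computed (for a 50-item category over three years, about 0.19, 0.91 and above 0.99 at 1%, 3% and 5% a year). But they rest on an assumed inflation rate, an SD borrowed from composition and a price test that the article does not plan, so they describe no planned analysis.

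The reply does not remove the point. The article is not silent on price: it makes price a main outcome and then states a measure for it, without a denominator, a deflator or a contrast. Which fields are captured at baseline is a design decision that later analysis can repair only if the photographs or price records happen to hold the information.

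**Conclusion.** The concern holds in this limited form: as described, a within-country change in mean food price cannot be separated from general inflation or from changes in pack size and product mix. On assumed inflation of 1% to 5% a year, the drift alone is about 3% to 16% over three years, and about 2% to 22% over the two- or four-year gaps that the analysis section implies. These ranges rest on the assumed rates only. The comparison with detectable changes also assumes an SD of 20 for price change, which the article gives only for composition. The conclusion does not depend on which survey schedule is correct, but the two conflict and must be reconciled.

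**What to change.** In the section on assessing food composition and price, add net pack weight or volume to the listed fields, and recover it from the pack photographs where it is readable.

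Under Data analysis and sample size:

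- Define the price outcome as price per 100 g or 100 mL, paired by product where the same product is found again.
- Deflate follow-up prices to baseline with the national consumer price index.
- Once the taxed or targeted categories are chosen, report as the main price result their change minus the change in untargeted categories in the same country. Fix the category lists before follow-up prices are examined. Taxes already in force at baseline do not make a category targeted unless the project changes them.
- Use one set of survey years in both sections.

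The contrast assumes that targeted and untargeted categories would have moved alike without the policy, and this should be stated. On a log scale a common deflator cancels out of the contrast, so deflation matters mainly for the change within each category and for any case without a usable untargeted category.

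The cost is one extra data field, a price index and a few sentences. The contrast has a slightly wider interval: on the assumptions above, the detectable difference goes from about 9.2% to 9.4%.

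### The paired composition change gives no weight to products that leave or enter the market, and the yearly means that would show such a shift carry no effect estimate

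*Protocol article*

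**What the plan says.** The Methods section of the Protocol article lists salt and sugar levels in foods among the main outcome measures. The section on assessing food composition and price gives the aim: "The objective of this survey is to measure and assess changes in salt and sugar levels in foods". Each round covers the shops that supply more than 80% of processed foods, so products that have disappeared or newly arrived are observed.

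The subsection Data analysis and sample size then names three analyses:

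- Descriptive means for each survey year: "Mean levels of salt and sugar, overall and by product category, and individual product prices and mean prices for each product category". These are not restricted to matched products.
- A change estimate: "We will estimate the paired change in salt and sugar levels between baseline data and each of the follow-up points".
- A model: "We will analyse the change over time using linear mixed models which account for the repeated measurements". Its random effects are not given.

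The same subsection says that "it is expected that data on around 1200 products will be collected each year", and claims "0.9 power to detect a 1% change in composition across all categories, or a 10% change for food categories with 50 items", taking an SD of 20 for the percentage change. It gives no number of products expected to be matched and does not mention turnover.

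The STICKE section lists candidate interventions from a preliminary stakeholder meeting. For the nutrient content of available foods it gives two routes: reformulation with industry, or "working with importing agencies to change the balance of imports" through nutrient content restrictions.

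**The concern.** The objective concerns levels in foods on the market. That level can change in two ways: products that stay on sale are reformulated, or the set of products on sale changes. A paired change measures the first and is blind to the second, because a delisted product has no follow-up value and a new one has no baseline.

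An import restriction based on nutrient content works mainly in the second way. If that route were chosen and succeeded, the one change estimate the protocol names could be close to zero. The converse also holds: matched products could improve while worse products come in, and the paired estimate would report only the improvement. Either way, the inferential result would answer a narrower question than the stated objective.

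**Working it through.** **Inputs.** From Data analysis and sample size: about 1200 products per survey, SD 20 for percentage change, 0.9 power for a 1% change overall or 10% in a 50-item category. Not in the document, so assumed: two-sided 5% level, share of products matched, share replaced (p), relative excess of the leaving products over the baseline mean (e), and within-product correlation (ρ).

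**1. The plan's own figure.** Paired power = Φ(δ√n/SD − 1.960).

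- n = 50, δ = 10: 10 × √50/20 = 3.536; Φ(1.576) = 0.94. This agrees with the stated 0.9. A two-sample formula with the same SD gives 0.71, so the statement is one about pairs.
- n = 1200, δ = 1: √1200/20 = 1.732; Φ(−0.228) = 0.41 (0.53 one-sided). The stated 0.9 is not reproduced. That is a separate matter and this point does not rest on it.

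**2. Products are not pairs.** The change detectable at 0.9 power is 20 × (1.960 + 1.282)/√n.

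| Share matched (assumed) | Pairs | Detectable change |
|---|---|---|
| 100% | 1200 | 1.87% |
| 80% | 960 | 2.09% |
| 60% | 720 | 2.42% |
| 40% | 480 | 2.96% |

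**3. Entry and exit without reformulation.** Set the baseline mean to 1.00, p = 0.20 and e = 0.30. New products sit at the baseline mean and surviving products do not change.

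- Survivors average (1.00 − 0.20 × 1.30)/0.80 = 0.925.
- Follow-up mean = 0.80 × 0.925 + 0.20 × 1.00 = 0.94, a fall of 6% (that is, p × e).
- Paired change = 0.

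**4. Would the mixed model recover it?** Assume a product random intercept, equal variance at both rounds and equal numbers of products. The time effect then weights the matched difference by (1 − p)/(1 − ρ) and the unmatched difference by p. With a matched difference of 0 and an unmatched difference of −e, the estimate is −p·e / [(1 − p)/(1 − ρ) + p].

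- ρ = 0.8: −0.06/(4.0 + 0.2) = −1.4%.
- ρ = 0.9: −0.06/(8.0 + 0.2) = −0.7%.

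Over a range of turnover, with e = 0.30:

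| p | Market mean | Paired | Model, ρ = 0.8 | Model, ρ = 0.9 |
|---|---|---|---|---|
| 10% | −3% | 0 | −0.03/4.6 = −0.7% | −0.03/9.1 = −0.3% |
| 20% | −6% | 0 | −1.4% | −0.7% |
| 30% | −9% | 0 | −0.09/3.8 = −2.4% | −0.09/7.3 = −1.2% |

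The fraction recovered does not depend on e. At p = 20% it is 1/4.2 = 24% for ρ = 0.8 and 1/8.2 = 12% for ρ = 0.9.

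**5. A simulated data set with different assumptions.** It has 1200 products, mean 500, between-product SD 200 and within-product SD 50, so ρ = 200²/(200² + 50²) = 0.94. The top 20% by salt are replaced by products like those remaining, with no reformulation. The all-product mean changed by −14.7%, the paired change was −0.3% (true value 0), and the random-intercept model gave −1.4%.

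**6. Precision of an all-product estimate.** With matched share s and N products per round, the variance of the difference in means is 2σ²(1 − sρ)/N. For the matched change it is 2σ²(1 − ρ)/(sN). At s = 0.8:

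- ρ = 0.8: 0.36 against 0.25, so the standard error is √1.44 = 1.2 times as large.
- ρ = 0.9: 0.28 against 0.125, so it is √2.24 = 1.5 times as large.

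**The case against.** The best defence is that the plan is not confined to pairs. Yearly means over all products, overall and by category, are planned, and the 6% fall in the illustration would appear there. The mixed model may include products seen once. Brand and manufacturer are recorded to find the imported share, and the composition data feed the dietary software, so a changed product mix can reach the intake outcomes. A reader might infer that the project would be blind to a shift in product mix; the documents do not support that. What stands against the defence is narrower: the means are only to be calculated, with no estimate or test of their change.

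A second defence is that model detail belongs in an analysis plan that is not shown. This stands for the random effects: the article does not specify a random intercept, so steps 4 and 5 are conditional on one. It does not stand for the paired change and its power basis, which the article states.

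Third, a reader might take the import restrictions as planned. They are not: they are one of two routes within one of three policy groups, and the impact evaluation section depends on what each country implements. The paired estimate suits the other route, reformulation, well.

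Finally, an all-product change mixes policy effects with other changes in assortment, whereas the paired change holds product identity fixed. That is a good reason not to replace one with the other.

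**Conclusion.** The point holds in a limited form. The named change estimate and its power statement rest on matched products, while the objective concerns foods on the market and one candidate intervention acts through products without a pair. A shift in mix would be seen descriptively but would have no effect estimate attached.

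Under the assumed 20% turnover and 30% excess, a 6% fall in the market mean corresponds to a paired change of 0, and to between −1.4% and −0.7% from a random-intercept model at correlations of 0.8 to 0.9. Turnover, excess and correlation are all assumptions; the document gives none of them. If little turnover occurs, or only reformulation is pursued, the gap is small.

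It does not follow that the paired analysis could show an effect when the only change is the entry of unhealthy products: they have no pair, so the paired change would stay at zero. Nor does it follow that the paired estimate is wrong for reformulation.

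**What to change.** Keep the matched-product change and label it the reformulation component. Beside it, report as an effect estimate the change in mean salt and sugar over all products present at each round, overall and by category, with a confidence interval and standard errors clustered by product. Put both on one scale (for example per 100 g, or as a percentage of the baseline category mean) and report their difference as the entry and exit component. State the expected number of matched products wherever power is quoted.

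The cost is a little more analysis on data already to be collected. The all-product interval will be wider, by roughly 20% to 50% under the assumptions of step 6, and it also picks up assortment changes unrelated to policy. For that reason both are reported and neither needs to replace the other.
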